
#### Procedures

After complying with the inclusion criteria, participants will be contacted via email to schedule their baseline evaluation, as well as be informed in advance about the conditions of the study, and that they must attend to the evaluation morning fasting and with an empty bladder. The day before the evaluation, participants will receive an email confirming the place, date, and time of their procedure, and a reminder of all the criteria they must fulfil to be assessed.

On the scheduled day, each participant will sign the free and informed consent and will be identified through an alphanumeric code (e.g., suf01), to maintain the anonymity of their information. Initially, it will be confirmed with each participant whether they remain fasting and if they have an empty bladder (as agreed in advance), and the information will be registered in a Microsoft Excel software file®. The start of the evaluation will be by the measurement of body mass (TANITA BC-601 scale), height (Seca, Hamburg, Germany), and waist circumference (according to the World Health Organization: the midpoint between the lower border of the rib cage and the iliac crest, after a normal expiration) [71]. The height measurement will be performed with the feet slightly apart, with nearby heels, a neutral spine position, and the head according to the Frankfurt plan.

After the measurement’s procedures, we will ask participants to remove all their metal belongings to evaluate their body composition, using BIA. They must lie in the supine position for about 5 min, with their legs slightly apart and arms along the body for placement of the electrodes in the standardized points (right hand and foot) [71], thus enabling the verification of reactance and resistance values. The postural evaluation will take place then, through two photos of the evaluated standing, and in two different positions (front and side), with the feet slightly apart at the width of the hip, relaxed shoulders, and spine in a neutral position. After an explanation of how to use the ActivPAL, the participants will receive the ActivPal device, which will be placed, with the aid of a waterproof pharmacological dressing, at the right thigh's midpoint.

It will be mentioned that the participant will have to use it for 7 consecutive days (without ever taking it off) from the day of the assessment and that the device will measure their PA, SB, and sleep, so it is essential that they maintain their normal routine. It will also be ensured that the participant does not perform any aquatic activity that maintains prolonged contact with water (e.g., diving, swimming). One day before the end of the period of use of the device, an email will be sent informing them about the place and time of the return of the device. Finally, the participant will fill out an online questionnaire, and in case of any questions, one trained evaluator can immediately assist. The questionnaire was built using *Qualtrics* online software, and it is divided into several blocks that involve different themes targeted for assessment, as previously stated. The questionnaire starts by presenting the informed consent (which the participant must agree with to fill the rest of the questionnaire), followed by relevant information about the participant, including the respective ID given by the technicians, the data collected in the on-site evaluation (their height, weight, and waist circumference), and some relevant sociodemographic information, as said before. Information about participants’ health and sedentary patterns will also be measured.

### Plans to promote participant retention and complete follow-up {18b}

Assessments will be conducted by the end of the intervention period and at the end of the follow-up. To maximize retention at all assessments we will:Send participants an advance reminder that measurements are upcoming, using a personalized email sent 2 to 3 weeks ahead of the measurement dates, complemented by a phone call to confirm/arrange an appropriate appointment time (suited to participants schedules).Send a confirmation of the date, time, and location (always inside the campus of the university, in a calm and adequate location).Text participant in the previous day leading up to their appointment to remind them about the time, date, and location.

To enhance overall adherence to assessment periods, feedback will be provided at the end, to all participants, assuring valuable personal information regarding participants sedentary patterns, body composition, eating patterns, health and work-related outcomes, fatigue, presenteeism, job satisfaction, well-being, and quality of life, and information on how these have changed over the course of the study. The control group will only receive that feedback on the second evaluation moment, as providing feedback on the baseline can influence their actions during the control phase, which is not desired.

The value, detail, and richness of the information provided via these assessments will be highlighted since the beginning of the study, for example in the dissemination contacts/explanation of the trial, as well as in the initial psychoeducational session. Furthermore, this initial session will highlight the importance of participation in the trial (description of how important RCTs are for science will be embedded in the information provided), and thus, reducing the risk of dropout. The control group (in higher risk of dropping out in the absence of intervention) will also be provided with the opportunity of having the intervention (waiting-list group) after the 6-month assessment period.

During the trial, a website will be nurtured with interesting information (i.e., short films highlighting the evidence-based benefits of sit-stand desk usage; shortcuts highlighting the several phases of the study with the inclusion of the participants (see Intervention description {11a} for more details).

### Data management {19}

Data entry, processing, and management will be done by two researchers supervised by the PI as follows steps:We will create a database with all measures obtained in data collection. An identification code will be generated for each participant to guarantee their privacy.A data set will be exported and saved by Qualtrics software containing all information obtained via questionnaires.We will also extract and save raw files based on ActivPAL information as well as a database will be created with PA, SB, and sleep information.A New database will collate and store anonymized data securely with all domains of the project.Data quality control will be accomplished by documentation checks, monitoring putative punching errors, and systematic controls.

### Confidentiality {27}

All collected data will be kept strictly confidential. The data obtained within the trial will be computerized and encrypted in a database, not containing any identifying elements of the participants. All participants will be given a unique ID number, nor by name (apart from the consent inform). This database will be maintained by those responsible for the investigation, on a secure server of CIDEFES-UL, for 10 years for research purposes only.

### Plans for collection, laboratory evaluation, and storage of biological specimens for genetic or molecular analysis in this trial/future use {33}

Not applicable.

## Statistical methods

### Statistical methods for primary and secondary outcomes {20a}

Statistical analysis will be performed using PASW Statistics for Windows version 28.0 (SPSS Inc., an IBM Company, Chicago IL, USA). Data will be analyzed for those having completed pre–post test data and using an intention-to-treat analysis. Baseline differences between the intervention and control group will be examined using independent samples *t*-tests. If exploratory analysis reveals a non-normally distribution for some variables, it will be alternatively used with the non-parametric tests. Repeated measures ANOVA, with time (baseline-M0, M1, and M2) as within-subjects factor and intervention condition as between-subjects factor, will be conducted to evaluate the effects of the intervention on primary and on secondary outcomes. Statistical significance will be set at *p* < 0.05.

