### Objectives {7}

This paper describes the protocol for a cluster randomized controlled trial (RCT) the Standing Up for Healthy Aging (SUFHA), which aims to evaluate the change in sedentary patterns (i.e., quantity and accumulation pattern) resulting from the introduction of a health-enhancing contextual modification (i.e., sit-stand desk) in the workplace, compared to a control group after 6 months of intervention (i.e., effectiveness). Secondary outcomes are body composition, eating patterns, health and work-related outcomes, skeletal muscle discomfort, well-being, and quality of life. Additionally, we aim to crossover the intervention and test the impact of 3 months without the sit-stand desks on sedentary patterns in the intervention group and the impact of 3 months of sit-stand desks in the control group, and the level of acceptance regarding the use of these sit-stand desks in both groups.

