### Sample size {14}

For cluster size and number calculation, we assumed that participants within the same workplace (cluster) would be independent, and therefore, an intra-cluster correlation of 0.01 will be used. Considering the main outcome of the present intervention (i.e., sitting time) and using an effect size of 0.80, the total number of participants for between-group analyses (control and intervention groups) with a power of 0.80 and a significance level of 0.05 (two-tailed test) would be 34 participants. Assuming a 20% dropout, we will conservatively recruit a total sample size of 40 participants (i.e., 20 controls and 20 in the intervention group).

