### Methods in analysis to handle protocol non-adherence and any statistical methods to handle missing data {20c}

Other than the intention-to-treat procedures, we will opt not to use any statistical artifact to handle missing data. We will, however, include more participants than needed (40 vs 34), anticipating some dropout or missing data during the trial.

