Besides the introduction of a contextual change in the workplace (i.e., sit-stand desk), this intervention will use an initial psychoeducational session to all participants, to inform about the harms of spending too much time sitting and the independent health benefits of interrupting this behavior more often. Furthermore, a motivational system of prompts will also be offered, nudging participants to stand more often, for 6 months. After the initial 6 months of the intervention, the control group will receive the sit-stand desk, and the intervention group will be without the stimulus, to observe if the new habits gained during the intervention period somehow remain after 3 months of follow-up (i.e., without the sit-stand desks). A major strength of the SUFHA is that it builds on previous interventions using sit-stand desks around the globe to target office workers in a university setting. Previous interventions have been combining sit-stand desk in addition to other strategies (i.e., multicomponent interventions) such as the usage of pedometer and/or competition among participants, or other strategies [79, 80], which makes it difficult to isolate the impact of simply using these sit-stand desks; SUFHA intends to fill this gap and extending it by providing data on maintenance of the new habits. Furthermore, feedback on the barriers and facilitators of the use of the sit-stand desks will also be collected via focus groups exploring the experiences of the participants during the trial.

The findings from this cluster RCT will provide insight for future research studies, as well as real-world interventions, and offer evidence for policy guidelines around workplace health and well-being.

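### The analysis set is ambiguous, missing outcomes have no stated method, and the three-visit ANOVA can remove people who have 6-month data

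*Protocol article*

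**What the plan says.** Three statements in the Protocol article bear on who is analysed.

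- Statistical methods {20a} gives the analysis set: "Data will be analyzed for those having completed pre–post test data and using an intention-to-treat analysis". It then names one model for primary and secondary outcomes: "Repeated measures ANOVA, with time (baseline-M0, M1, and M2) as within-subjects factor and intervention condition as between-subjects factor".
- The missing-data section {20c} adds: "Other than the intention-to-treat procedures, we will opt not to use any statistical artifact to handle missing data". Its stated safeguard is to "include more participants than needed (40 vs 34), anticipating some dropout or missing data during the trial".
- Retention {18b} identifies an arm-specific risk: "The control group (in higher risk of dropping out in the absence of intervention". The same sentence offers controls the desk after the 6-month assessment.

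The Objectives {7} place effectiveness at 6 months (M1). M2 follows 3 months later, under changed conditions. In the words of the Discussion, "the control group will receive the sit-stand desk, and the intervention group will be without the stimulus".

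**The concern.** Requiring post-test data excludes randomised participants because of something that happened after randomisation. Intention-to-treat means keeping them. The sentence in {20a} joins the two without saying how they relate, and {20c} closes off the usual means of reconciling them.

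The named model adds a second restriction. A standard repeated measures ANOVA uses only people with every level of the time factor. Someone with M0 and M1 but no M2 meets the pre-post rule, yet drops out of the model. The stated analysis set and the stated model therefore disagree with each other.

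The main 6-month answer is at stake. It could rest on a subset chosen partly by who attended at 9 months, when one arm has lost its desks and the other has gained them, and still be reported as intention-to-treat.

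**Working it through.** **Inputs.** From Sample size {14}: 34 required, 40 recruited, 20 per arm, 20% dropout, two-sided 5% level, and the calculation "using an effect size of 0.80". No SD is given, so I read 0.80 as a standardised mean difference. The timing and mechanism of dropout are not stated. I treat the 20% as the total loss by M2 and vary its timing.

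**Step 1: the plan's own figures.** 40 × (1 − 0.20) = 32, which is below the plan's 34. Going from 40 to 34 covers a loss of 6/40 = 15%. Keeping 34 after 20% loss would need 34/0.80 = 42.5, that is 43. The 34 is itself not reproduced by a two-sample comparison at d = 0.80 with 80% power: the t-test gives 52 and the normal approximation 50. That is a separate matter. The power values below should be read only as differences between scenarios.

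**Step 2: who is kept under each rule.**

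| Data observed | Intention-to-treat | Pre-post rule | Standard three-visit ANOVA | Mixed model, all available data |
|---|---|---|---|---|
| M0, M1, M2 | in | in | in | in |
| M0, M1 | in | in | out | in |
| M0 only | in | out | out | in |

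The second row matters for the 6-month contrast: the outcome has been measured but is not used.

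**Step 3: how many people, and what that costs.** Power is that of a two-sample t-test with n per arm, 2n − 2 degrees of freedom and noncentrality 0.80 × √(n/2). The noncentrality is 0.80 × √10 = 2.53 for n = 20, 0.80 × √9 = 2.40 for n = 18, and 0.80 × √8 = 2.26 for n = 16. The corresponding powers are 0.693, 0.645 and 0.591.

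| Timing of the 20% loss (8 of 40) | With M1 data | In the ANOVA | Extra loss | Power, all M1 data | Power, ANOVA set |
|---|---|---|---|---|---|
| All before M1 | 32 | 32 | 0 | 0.591 | 0.591 |
| 4 before M1, 4 after | 36 | 32 | 4 | 0.645 | 0.591 |
| All after M1 | 40 | 32 | 8 | 0.693 | 0.591 |

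These figures assume equal loss in both arms, a post-only comparison and no clustering. They are not the power of the planned ANOVA or of a mixed model.

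**Step 4: what bias could look like (assumed, not documented).** Within one arm, the completer mean minus the full-arm mean equals p × (completer mean − dropout mean), where p is the share lost.

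- With p = 0.20 and no difference between completers and dropouts, the bias is 0.
- With a difference of 0.5 SD, it is 0.20 × 0.5 = 0.10 SD, and 0.10/0.80 = 12.5% of the planned effect.
- If instead the log-odds of dropout rise by 0.5 to 1.0 per SD of the outcome, with 20% lost overall, the completer mean shifts by about 0.10 to 0.17 SD.

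These shifts reach the arm contrast in full only if dropout in the other arm is random. If the same mechanism acts equally in both arms, they cancel. Recruiting more people changes neither p nor the difference, so it does not reduce the bias.

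**The case against.** The {20a} sentence can fairly be read as two analyses, one on completers and one by intention-to-treat. Section {20c} supports this, because it treats the intention-to-treat procedures as something separate and exempts them. An article may also leave their detail to a fuller document. It stands, then, that the text does not prove a completers-only plan. But neither analysis is named as primary, and no section says how a participant without outcome data would enter the second one. Beyond those undefined procedures, {20c} refuses any method, so a fuller document would have to override that statement rather than fill a gap.

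Listwise deletion is inferred from the method and is not stated. The Dissemination plans {31a} foresee separate papers for intervention and follow-up results, so an analysis of M0 and M1 alone may be intended. That is possible, but {20a} names only the three-level model. The dependence on M2 is therefore a risk of following the text, not a certainty.

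On bias, {18b} names a recognised risk and a countermeasure. It does not forecast unequal dropout. Even unequal rates would not show that dropout depends on the outcome. This objection stands in full.

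Finally, if all dropout precedes M1, the ANOVA discards nothing extra. That also stands, which is why the size is given as a range.

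**Conclusion.** The point holds as an ambiguity that needs correcting before analysis. The relation between the completer set and intention-to-treat is not fixed, intention-to-treat is undefined, and the one model named can discard observed 6-month outcomes because of a later visit. At the planned 20% dropout the ANOVA would use 32 of 40. Compared with using all M1 data, the extra loss is 0 to 8 people, worth 0 to about 10 percentage points of illustrative power (0.693 − 0.591 = 0.102). This rests on the standard form of repeated measures ANOVA, on 20% being the total loss by M2, and on an unadjusted t-test at d = 0.80.

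A reader might infer two stronger things. The first is that the plan analyses only completers and mislabels them as intention-to-treat. The sentence allows that reading but equally allows two analyses. The second is that completers are a non-random subset, so that the 6-month result is biased. The protocol gives no evidence that dropout depends on the outcome. What can be said is that bias is possible, that the plan has no method to address or probe it, and that over-recruitment would not remove it.

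**What to change.** In {20a}, define the primary analysis as all randomised participants in their allocated arms. Use a likelihood-based linear mixed model on all available M0, M1 and M2 values, with a random effect for the randomised cluster (sites, or workers who can observe each other, per {16a}). Make the arm contrast at M1 primary and not conditional on having M2. Make the M2 contrast secondary, so that the follow-up objective keeps a model. Label any completer analysis as supplementary.

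In {20c}, replace the refusal of missing-data methods with a statement that the model assumes data are missing at random. Add one sensitivity analysis that shifts missing M1 values by arm (delta adjustment). Both changes are needed: the mixed model removes attrition bias only under missing at random, and the delta analysis probes departures from it.

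The cost is revised wording and slightly more analysis work in the same software, with no new data. The Trial status section reports two assessments still to come at that version, so the change could be made before those outcomes were known.

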### Interim analyses {21b}

The intervention was considered low risk, and therefore, interim analyses and formal stopping rules were not deemed necessary by the research team. However, the study protocol will include monitoring for adverse events via an online form that will be periodically reviewed to ensure participant safety.

### Methods for additional analyses (e.g., subgroup analyses) {20b}

Not applicable. We will probably not have enough sample size to allow subgroup analyses.

### Methods in analysis to handle protocol non-adherence and any statistical methods to handle missing data {20c}

Other than the intention-to-treat procedures, we will opt not to use any statistical artifact to handle missing data. We will, however, include more participants than needed (40 vs 34), anticipating some dropout or missing data during the trial.

### Plans to give access to the full protocol, participant-level data, and statistical code {31c}

Public access to the full protocol is granted by the registration in a public online platform https://doi.org/10.17605/OSF.IO/JHGPW and also by the SUFHA website http://sufha.ulusofona.pt/.

## Oversight and monitoring

### Composition of the coordinating center and trial steering committee {5d}

A Steering Committee will be formed at the beginning of this study for monitoring the trial. This committee will be led by the PI, in a small group to run smoothly in monitoring the activities under trial. The Steering Committee will meet every week with the research team to analyze the study progressions and to propose counter measures when deviations occur from the established trial plan.

### Composition of the data monitoring committee, its role and reporting structure {21a}

A data monitoring committee will not be needed for the SUFHA trial, given that both interventions are non-invasive with minimal risk of harm. Regardless, the research team will meet once a week to discuss participants and intervention progress, emerging challenges and required adjustments to the protocol.

### Adverse event reporting and harms {22}

Although the known risks of using sit-stand desks are low, SUFHA has the following procedures to report such events.

An adverse event (AE) is any negative event reported by a participant or observed by the investigator during the trial, which may not be related to the intervention. All AEs will be recorded in a form by the research team with information about severity, frequency, date of onset, duration, and action taken, as well as the relationship between the AE and the intervention and the participant outcome. Participants will be instructed to communicate to the research team any discomfort or unexpected adverse reaction to using the sit-stand desk.

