## Interventions

### Explanation for the choice of comparators {6b}

SUFHA is designed for a sample of adult University office workers and will consist of two groups. A waiting-list control group will only attend a psychoeducational session regarding the independent benefits of reducing and interrupting sitting time with standing, with no contextual change during the 6-month intervention (i.e., no access to the sit/stand desk). The intervention group will attend the psychoeducational session and will be provided with the opportunity to have a sit-stand desk in their workplace, allowing them to work seated or standing and change between these postures as many times as they desire for 6 months.

After the intervention period, the waiting-list control group will have access to the sit-stand desk.

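### Participants are told to report reactions to the sit-stand desk, although an adverse event is defined as any negative event, so spontaneous reports risk differing by arm

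*Protocol article*

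**What the plan says.** The section on adverse event reporting and harms (item 22) opens by tying its procedures to the desk: "Although the known risks of using sit-stand desks are low, SUFHA has the following procedures to report such events". It then gives a broad definition that is neutral between the arms and requires no causal link: "An adverse event (AE) is any negative event reported by a participant or observed by the investigator during the trial". Recording is equally broad: "All AEs will be recorded in a form by the research team with information about severity, frequency, date of onset, duration, and action taken", along with relation to the intervention and outcome. The section closes with the only instruction to participants that it states: "Participants will be instructed to communicate to the research team any discomfort or unexpected adverse reaction to using the sit-stand desk".

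Three other parts of the article bear on how that instruction works in practice:

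- **Exposure.** Under the choice of comparators (6b), controls spend the first 6 months "with no contextual change during the 6-month intervention (i.e., no access to the sit/stand desk". They receive the desk for the 3-month follow-up, while the intervention arm loses it (6b, 11a and the Discussion).
- **Blinding.** Under item 17a, neither participants nor staff are blinded once baseline is complete.
- **A second route.** Under interim analyses (21b), "the study protocol will include monitoring for adverse events via an online form that will be periodically reviewed to ensure participant safety". The article does not limit this form to desk reactions or to one arm.

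**The concern.** What is to be counted and what participants are asked to report are not the same thing. Someone without a desk who develops back pain, headache or an unrelated illness has an adverse event under the definition, but has no reaction to a desk to report. For the first 6 months that describes the whole control arm. The gap between definition and instruction therefore falls along allocation, in a trial where everyone knows the allocation.

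At stake is how any listing of adverse events by arm can be read. The trial has no data monitoring committee (21a), safety oversight rests on the research team's review of these reports (23), and the Discussion hopes to persuade employers to invest in the desks. If reports come mainly from people prompted about a desk, the record gives no sound background rate from usual seated work against which to set them.

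**Working it through.** The article states no event rate, capture rate or safety power, so there is no figure to reproduce. The check sets the relevant statements side by side and then uses assumed values to show scale.

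**Step 1: definition against instruction.** The definition (22) covers any negative event, related or not, in any participant. The instruction (22) covers discomfort or reactions to using the desk. On its natural reading, it asks a person without a desk for little or nothing.

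**Step 2: who has the desk, and when.** Up to the 6-month assessment (M1), the intervention arm only. From M1 to the end of follow-up (M2), the control arm only. Any distortion would therefore reverse at M1.

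**Step 3: do the other routes clearly close the gap?**

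- *Events observed by staff (22)* depend on contact. The intervention arm has more of it: desk installation, a demonstration, individual guidance and repeated nudges (11a).
- *The online form (21b)* could close the gap if it puts a neutral question to both arms. The article does not show that it does. Item 22 describes a form completed by the research team, so the online form may only log what has already been reported.
- *The Nordic questionnaire (18a)* is given to both arms at the same time points (12, 13). It covers the prior week only, at baseline, the final intervention month and the final follow-up month. It therefore misses complaints that come and go between visits, including those while users build up standing time.

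**Step 4: scale, on assumed values.** Take n = 20 per arm (item 14), the same true risk p in both arms, and capture probabilities s_D with a desk and s_N without. Then:

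- expected recorded events = n × p × s
- recorded risk ratio = s_D / s_N
- recorded risk difference = p × (s_D − s_N)

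With p = 0.2 and s_D = 0.9 (both assumed):

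| s_N | Recorded events, desk arm | Recorded events, no-desk arm | Risk ratio |
|---|---|---|---|
| 0.9 | 20 × 0.2 × 0.9 = 3.6 | 3.6 | 1.0 |
| 0.6 | 3.6 | 2.4 | 1.5 |
| 0.3 | 3.6 | 1.2 | 3.0 |

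With s_N = 0.3, the spurious risk difference runs from 0.1 × 0.6 = 0.06 at p = 0.1 to 0.5 × 0.6 = 0.30 at p = 0.5. Other assumptions give other ratios: capture of 0.80 against 0.40 or 0.20 gives 2.0 or 4.0.

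**Step 5: why the two periods need separating.** Assume a constant monthly event rate and capture of 0.9 with a desk and 0.3 without. Over 9 months the intervention arm records in proportion to 6 × 0.9 + 3 × 0.3 = 6.3, and the control arm to 6 × 0.3 + 3 × 0.9 = 4.5. The ratio is 6.3 / 4.5 = 1.4. That single figure hides a ratio of 3.0 up to M1 and 0.33 after it, with no true difference in either period.

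**The case against.** The best reply is that the instruction is one sentence in a wider scheme. All events are to be recorded, including those staff observe and those unrelated to the intervention. The online form is a second route that is not confined to the desk. Events are reviewed at weekly meetings (23). The instruction is addressed to all participants, and its first words can be read as covering any discomfort at all. The article also condenses a fuller protocol, so the form's wording, recipients and dates may be settled there, and their absence here is no fault.

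Much of this stands, and it rules out three stronger readings that a reader might infer:

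- *That events are asked about solely as desk reactions, and so are under-recorded in controls.* The article does not support this. The online form may already put a neutral question to both arms. What the text shows is a risk.
- *That the trial's safety comparison is biased.* No such comparison is planned. The statistical methods (20a) cover primary and secondary outcomes, and adverse events are neither. The point applies to any table of events by arm.
- *That the trial cannot say whether musculoskeletal complaints differ from usual seated work.* It can, at the assessments: discomfort is a secondary outcome measured by questionnaire in both arms and analysed between them.

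What the reply does not remove is the mismatch within item 22. It lies in what the section states, not in what an article leaves out, and the other routes are not shown to correct it.

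**Conclusion.** The point holds as a risk of unequal reporting. The stated instruction is narrower than the stated definition, the difference follows desk access, and desk access follows allocation and then reverses at M1. In an unblinded trial, spontaneous reports may therefore differ by arm without any difference in true rates, and a table of events by arm could overstate harm in whichever arm has the desk.

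The size cannot be determined from the document. The ratios of 1.0 to 3.0, and 2.0 to 4.0 under the other assumptions, are ratios of assumed capture rates. They show how the distortion would behave, not how large it is. If the online form already asks both arms a neutral question on the same dates, the distortion could be absent. The primary outcomes come from the ActivPAL and are unaffected. This is a modest weakness in the harms plan that is cheap to remove.

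**What to change.** Make the instruction in item 22 match its definition. Ask both arms the same question, with no mention of the desk, such as whether there has been any new or worse health problem since the last contact. Send it on the same dates to everyone, for example through the online form in item 21b, and repeat it at M1 and M2. Have the investigator judge relation to the desk afterwards, rather than leave participants to screen events by cause before reporting.

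Report counts by allocated arm, separately for the period up to M1 and the period after it. The article describes the intervention as under way with two assessments still to come. If participants have already been given the instruction as written, record the date of the change and read counts by arm from before it with caution.

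The cost is small: one question, and a few more unrelated events to record. If the existing form already works this way, only the sentence in item 22 needs to change.
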